### Randomisation and intervention assignment methods

#### Sequence generation

The randomisation sequence will be generated by a statistician using Stata software. Randomisation will be stratified by site and blocked, and participants will be randomised using a 1:1 algorithm to ensure an equal number of participants in the treatment and control arms.

#### Allocation concealment mechanism

Allocation concealment will be ensured as the randomisation code will not be released until the IAPT service user has been recruited into the trial, which takes place after participant eligibility has been assessed, participant identifier has been recorded, and consent gained to take part in the trial and to being randomly allocated to treatment condition.

#### Implementation

Randomisation will be requested via RedCap by the researcher who recruited and consented the participant into the trial. RedCap will send a response to the researcher informing them which treatment the participant will be receiving. Randomisation can only be requested once and after participant identifier, eligibility and consent have been recorded, and therefore, implementation cannot be influenced by the PWP, participant, the research or clinical team.

### Blinding

Due to the nature of the intervention, it is not possible to blind participants and PWPs who deliver the intervention. Quantitative 3 month follow-up outcome assessments will be conducted by a researcher who will be blinded to treatment allocation. Qualitative interviews will be conducted after quantitative outcomes assessment, as it is possible that the researcher will become unblinded during interviews. Outcome assessor blinding will also be verified by self-report at final follow-up.

### Data collection

See Additional file 1 for full data management plan.

#### Quantitative data collection

Table 1 and Fig. 1 present a schedule of data collection. Most participant data will be collected as part of usual care. Baseline and 3 month follow-up data will be collected by a researcher. Usual care data will be recorded by PWPs using patient management software and then extracted and input into RedCap by researchers (Table 3).

**Table 3 Tab3:** List of variables, and who the variables will be collected by

Category	Variable	Collected by who*	Are data collected as part of routine care?
Eligibility	Eligibility criteria met	Researcher	No
Demographics	Date of birth	PWP/researcher	Yes
	Ethnicity	PWP/researcher	Yes
	Gender	PWP/researcher	Yes
	Education	PWP/researcher	Yes
Mental health	Comorbid mental health conditions	PWP/researcher	Yes
	PHQ-9	PWP/researcher	Yes
	GAD-7	PWP/researcher	Yes
Smoking	Smoking status	PWP/researcher	Yes, but not regularly
	Smoking history	PWP/researcher	No
	Cigarettes per day	PWP/researcher	No
	Bio-verification of smoking status	Researcher	No
	Smoking cessation medication used in intervention	PWP	No
Service	Participant drop-out of IAPT	PWP	Yes
	Planned, completed and missed IAPT appointments	PWP/researcher	Yes
Acceptability and feasibility	Retention in smoking cessation intervention	PWP	No
	Participant satisfaction with smoking cessation intervention	PWP/researcher	No
	Clinician satisfaction with smoking cessation intervention	Researcher	No
	Qualitative Interviews	Researcher	No
Implementation	Audio recording of treatment session	PWP	Yes
	Intervention implementation checklist	Researcher	No

**PWP* = Psychological wellbeing practitioner

#### Qualitative data collection

We will collect two types of qualitative data:Audio recordings of intervention deliveryPost-intervention interviews with PWPs and participants

Intervention delivery audio recordings will be taken as part of usual care, and only relevant sections, as decided by a researcher, will be used for analysis (i.e., where smoking cessation treatment is being delivered). We will have access to these recordings and will sample 30 random sessions to assess implementation.

Interviews will be conducted by a researcher, ideally in-person, but also over the telephone upon request. Interviews will last no longer than 60 minutes and will be conducted using flexible topic guides to ensure that the same broad topics are covered in all interviews, while allowing flexibility for interviewees to introduce new issues [41]. Topic guides will be modified as necessary throughout the course of the interviews to reflect findings as they emerge. The interviewer will use open-ended questioning techniques to elicit participants’ own experiences and views, and participants will be asked to provide examples to avoid reliance on ‘hypothetical’ accounts. Interviews will be anonymised to protect confidentiality. All interview data will be transcribed using a university-approved service.

### Post-trial care

If the participant would like to use smoking cessation medication/products beyond their IAPT treatment, they will be able to obtain a prescription from their GP or local smoking cessation service. Participants will be required to pay a prescription dispensing fee, unless they are exempt from paying for their prescriptions through the NHS. If the participant was not successful in their quit attempt, the PWP will provide them with contact details to a local stop smoking service.

### Adverse events

PWPs will check in with participants about the progress of their quit attempt and the stop smoking medication/products that they are using. In the case that a participant is experiencing any unusual symptoms or events, PWPs will use the NHS ‘Decision Tree for Adverse Event Reporting’ (see Additional file 1) to class and action adverse events (i.e., any unfavourable and unintended signs, symptoms or a disease associated with treatment). Adverse event(s) will be recorded in the study file with a note that will identify when the event occurred, the details of the adverse event(s), any potential study relation, action taken and resolution/closure of the adverse event(s). An assessment of seriousness will be made and will be reported to the Chief Investigator and a Research Governance Officer.

### Patient and public involvement

During study conceptualisation, the research aims and study design were peer-reviewed by several members of the public, and were presented to the UK Centre for Tobacco and Alcohol Studies Smokers’ Panel and the Elizabeth Blackwell Institute’s Public Advisory Group for feedback. In general, the study’s concept was well received, understood, and thought to be an important area of research. We will invite a patient member to trial management meetings and involve patient and public panels in analysis and dissemination.

### Participant benefit

By taking part in this research, participants will assist in the design and planning of an intervention to help others quit smoking. Also, by choosing to take part, participants will increase their chances of quitting smoking, which is the single most important change one can make to improve their health.

### Quantitative analysis

Analyses will be conducted using Stata software.

#### Primary and secondary feasibility measures

We will present the number of participants who were screened, randomised, treated, and followed up for primary outcome in a CONSORT-style flow chart. The proportion of study completers, by trial arm, will be calculated as:$$ \frac{N\ \mathrm{study}\ \mathrm{completers}}{N\ \mathrm{randomised}\ \mathrm{at}\ \mathrm{baseline}} $$

#### Piloting main trial outcomes

The outcome measures which we intend to include in the main trial will be piloted in this feasibility study. We will present summary statistics by trial arm for each measure at baseline and 3 month follow-up. Estimated intervention effects will be presented with 95% confidence intervals, these estimates being calculated using regression models that include study site, the patient’s PWP and baseline GAD-7 and PHQ-9 scores. Linear regression will estimate differences in means for continuous measures, and logistic regression will estimate odds ratios for binary measures. As this is a feasibility study, these estimates will be too imprecise to support definitive conclusions, but will be inspected for evidence of a benefit of combining the smoking cessation treatment programme  with IAPT usual care.

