### Setting

This is a multicentre study involving two Improving Access to Psychological Therapies (IAPT) sites in the UK (i.e., Bristol and Oxford). IAPT is a NHS primary-care based psychological therapy service (https://www.england.nhs.uk/mental-health/adults/iapt/). IAPT offers low- and high-intensity evidence-based therapies (e.g., cognitive behavioural therapy (CBT)) to people with common mental disorders. Psychological treatment is delivered by therapists named ‘psychological wellbeing practitioners’ (PWPs) and usually consists of six 30–45-minute sessions, delivered over the telephone or face-to-face (further details below).

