### Control arm

Participants in the control arm will receive IAPT usual care, plus contact details for their local smoking cessation service during their final IAPT appointment.

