### PWP training programme

A maximum of ten PWPs per site will be trained to deliver the treatment. PWPs will take part in the following training:NCSCT level 1 online training and assessment programmeNCSCT level 2 face-to-face trainingAn overview about the importance of randomised trial methodology and study procedures (e.g., data recording)A researcher will visit each service once a month to listen in sessions and offer feedback to PWPs

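### Entering each patient's therapist (PWP) as a covariate in the logistic model for quitting discards a large share of participants and exaggerates a real odds ratio

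*Protocol article*

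**What the plan says.** All references are to the protocol article.

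- **Piloting main trial outcomes.** Effects come from "regression models that include study site, the patient’s PWP and baseline GAD-7 and PHQ-9 scores". The model types are given in the next sentence: "Linear regression will estimate differences in means for continuous measures, and logistic regression will estimate odds ratios for binary measures". No random effect, clustered variance or penalised fit is named. The same section warns that the estimates are too imprecise for firm conclusions, but says they will be looked at for signs of benefit.
- **Setting** and **PWP training programme.** There are "two Improving Access to Psychological Therapies (IAPT) sites in the UK", and "A maximum of ten PWPs per site will be trained to deliver the treatment". The ceiling is therefore 2 × 10 = 20 trained PWPs.
- **Sequence generation.** "Randomisation will be stratified by site and blocked", and "participants will be randomised using a 1:1 algorithm". PWP is not a stratification factor.
- **Control arm.** "Participants in the control arm will receive IAPT usual care", plus contact details for a local stop-smoking service. The section does not say whether the trained PWPs or other PWPs deliver that care.
- **Sample size, Trial.** 100 participants are assumed at follow-up, from 157 at baseline.

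**The concern.** A logistic model with one term per PWP needs both quitters and non-quitters among each PWP's patients. With up to 20 PWPs, 100 participants and few quits, many PWPs will have no quitter. Their terms have no finite estimate, and their patients tell the model nothing about the arm effect. Among those who remain, many terms are fitted to few events, which moves a maximum-likelihood odds ratio away from 1.

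Quitting is one of the outcomes being piloted for the main trial. Its adjusted odds ratio could rest on little more than half of the participants and look larger than it is. The warning about imprecision does not cover this, because systematic exaggeration is a different fault from a wide interval.

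**Working it through.** **Reproducing the plan's figures.** 100 / (1 − 0.36) = 156.25, rounded up to 157, as stated. The exact 95% interval for 20 of 50 is 26.4% to 54.8%, matching the stated 26% to 55%. So 100 analysed, about 50 per arm, is the plan's own basis.

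**Site and PWP together.** With 20 PWPs nested in two sites, the columns are intercept 1 + arm 1 + site 1 + PWP 19 + two scores = 24. The rank is 23, because site is an exact sum of PWP indicators. Removing site leaves the rank at 23, so one term is redundant and the arm estimate is unchanged.

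**Different PWPs in each arm (hypothetical).** The rank is 22 with the arm term and 22 without it. Arm is then a combination of PWP indicators, and no effect is estimable in either the linear or the logistic model.

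**Shared PWPs: participants lost.** Assume patients fall at random on K PWPs, with n = 100 and overall quit rate p (the mean of the two arms). A patient is uninformative if everyone with the same PWP has the same outcome:

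P = (1 − p)(1 − p/K)^(n−1) + p(1 − (1 − p)/K)^(n−1)

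- p = 0.15, K = 20: 0.85 × 0.9925^99 + 0.15 × 0.9575^99 = 0.403 + 0.002 = 0.405
- p = 0.15, K = 10: 0.85 × 0.985^99 = 0.190, with a negligible second term

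**Shared PWPs: the odds ratio.** Simulation of 1,500 trials per scenario: n = 100, 1:1 allocation, no true PWP effect, PWPs without outcome variation dropped. The article gives no quit rates, so those below are assumptions and a range is shown.

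| Quit rates | True OR | Median OR, 20 PWPs (mean excluded of 100) | Median OR, 10 PWPs (mean excluded) | Median OR, site and scores only (20-PWP runs) |
|---|---|---|---|---|
| 5% v 10% | 2.11 | 2.56 (64) | 2.38 (44) | 2.13 |
| 5% v 15% | 3.35 | 4.84 (55) | 4.13 (33) | 3.54 |
| 10% v 20% | 2.25 | 2.96 (40) | 2.65 (19) | 2.38 |
| 15% v 25% | 1.89 | 2.37 (30) | 2.09 (11) | 1.98 |

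Repeat runs at 10% v 20% give about 2.9 and 2.6, so the second decimal is simulation noise. The exclusions agree with the formula.

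- Size at 10% v 20% with 20 PWPs: 2.96 / 2.25 = 1.32, against 2.38 / 2.25 = 1.06 without PWP terms.
- Spread in that scenario: the SD of the log OR is 0.99 with PWP terms and 0.67 without.
- Failed fits at 5% v 10% with 20 PWPs: 14% with PWP terms, 9% without.
- With 156 analysed and 20 PWPs at 10% v 20%: median 2.60, with 41 excluded.
- Coverage of the 95% interval with PWP terms: 93% to 98%.
- No true effect (10% or 15% in both arms, 10 or 20 PWPs): median OR 0.96 to 0.98, with rejection in 3% to 6% of trials.

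**Linear models with shared PWPs.** These remain estimable and unbiased. Replacing one site term by 19 PWP terms costs 18 degrees of freedom.

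**The case against.** The strongest reply is that a model can include PWP as a random intercept, that the article is a condensed document, and that it promises a full statistical plan before analysis. This stands in part: the later plan could put the matter right. But the article names only linear and logistic regression and lists PWP beside site and the baseline scores. The plain reading is a covariate, so the later plan would have to change the stated model and not merely fill in a detail.

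Other parts of the reply stand in full. Twenty PWPs is a ceiling, and with ten the exaggeration is smaller. Interval coverage stays acceptable. Summary statistics by arm will be shown for each measure, so the raw quit proportions stay visible. The main outcome, the proportion of completers, uses no regression, and no stated decision depends on the quit odds ratio.

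Four stronger readings are tempting, and the article does not support them:

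- *The arm effect cannot be estimated.* That holds only if the arms have different PWPs, and the article is silent on who treats controls.
- *PWP is assigned as part of delivering the arm, so it is not a baseline factor.* The article does not say when PWPs are assigned.
- *Having both site and PWP breaks the model.* Software drops one redundant term and the arm estimate is unaffected.
- *The model would manufacture a benefit.* Under no effect the median stays near 1. The bias enlarges a real effect and does not create one.

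**Conclusion.** The point holds at moderate severity and for secondary pilot estimates only. With PWP as a categorical covariate, 100 followed up and PWPs shared by both arms, the quit odds ratio is exaggerated by roughly 20% to 45% with 20 PWPs across the assumed quit rates. About 30 to 64 of the 100 participants contribute nothing to it. At 10% v 20% the median is about 2.9 with 20 PWPs or 2.6 with 10, against a true 2.25.

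These sizes rest on assumed quit rates, random spread of patients over PWPs and no true PWP effect. The continuous outcomes lose only degrees of freedom if PWPs are shared. If they are not shared, the stated model with PWP fixed gives no arm effect for any outcome, so the article fixes a model whose usability depends on a fact that it does not give. The completer proportion and the sample size are untouched.

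**What to change.** Change the model sentence under Piloting main trial outcomes:

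- Adjust for study site (the stratification factor) and baseline PHQ-9 and GAD-7, and remove PWP as a fixed covariate.
- Treat PWP as a clustering factor for both continuous and binary outcomes, by a random intercept or PWP-clustered standard errors, in both arms where PWPs treat both. With 20 clusters or fewer, clustered standard errors need a small-sample correction.
- Report the between-PWP intraclass correlation descriptively, for planning the main trial.
- State whether the trained PWPs also treat control patients.

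The cost is a sentence or two. The downside is small: differences between PWPs move into the error term, and the intraclass correlation will be imprecise at this size. In the simulations, the model without PWP terms excluded nobody for lack of outcome variation within a PWP, and its median at 10% v 20% was 2.38 against 2.25.

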#### We will check data completeness for the following outcomes

Smoking-related:Carbon monoxide (CO)-verified 7-day point prevalence smoking cessation (i.e., validated by exhaled carbon monoxide concentration of < 10 ppm (ppm) [34]. CO-testing will be available on both sites via a 3 month follow-up home visit.Number of cigarettes per day (CPD)Heaviness of Smoking Index (HSI) [35]

Mental health-related:Patient Health Questionnaire (PHQ-9) [36] score

Service-related:Number of ‘Did Not Attends’Number of planned, completed and missed IAPT appointments

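### The linear models for cigarettes per day and HSI omit their own baseline values, giving up precision and leaving in chance imbalance that available data could remove

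*Protocol article*

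**What the plan says.** The section Piloting main trial outcomes describes the comparative analysis in a few sentences.

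- **Covariates.** All regression models include study site, the patient's PWP and "baseline GAD-7 and PHQ-9 scores". The list is not varied by outcome.
- **Model types.** "Linear regression will estimate differences in means for continuous measures", and "logistic regression will estimate odds ratios for binary measures".
- **Baseline data.** "We will present summary statistics by trial arm for each measure at baseline and 3 month follow-up". Under Quantitative data collection: "Baseline and 3 month follow-up data will be collected by a researcher". Table 3 there lists cigarettes per day and smoking history among the collected variables.
- **Outcomes.** The outcomes checked for data completeness include three smoking measures (CO-verified 7-day abstinence, CPD and HSI) and one mental health measure (PHQ-9).
- **Randomisation.** "Randomisation will be stratified by site and blocked", with 1:1 allocation. No smoking variable is a stratification factor.
- **Role of the estimates.** The article calls them too imprecise for definitive conclusions, but will look at them for signs of benefit. It promises a full statistical plan before the analysis.

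**The concern.** The covariate list suits the mental health outcome and not the smoking outcomes. PHQ-9 gets its own baseline value. GAD-7 is a covariate although it is not among the listed outcomes. CPD and HSI get no baseline smoking measure at all.

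How much someone smokes at entry is the natural predictor of how much they smoke three months later. Eligibility asks for daily smoking for at least a year and sets no minimum or maximum consumption, so baseline levels may vary widely. Site stratification does nothing to balance them. In a trial of this size the CPD and HSI contrasts would therefore carry avoidable noise, and any chance difference in baseline smoking would pass into the estimate in proportion to the baseline-to-follow-up correlation.

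**Working it through.** **1. The number per arm, from the plan's own figures.** The Sample size section assumes 100 participants at follow-up and gives 26% to 55% around 40% retention in the intervention arm. The exact (Clopper-Pearson) interval for 20 of 50 is 26.4% to 54.8%, so the plan is counting 50 per arm. The baseline number also reproduces: 100 / (1 - 0.36) = 156.25, rounded up to 157.

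**2. Precision for CPD and HSI.** Take n = 50 per arm and outcomes in SD units, where SD is the residual SD given the stated covariates. Let rho be the partial correlation between baseline and 3-month values given those covariates. The documents give neither an SD nor a correlation, so rho is an assumption and a range is shown.

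- Half-width without the baseline value: 1.96 × sqrt(2/50) = 0.392 SD.
- Half-width with it: 0.392 × sqrt(1 - rho²).
- Equivalent sample size: 100 / (1 - rho²).

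| rho (assumed) | Variance reduction | CI width multiplier | Half-width (SD) | 100 participants worth |
|---|---|---|---|---|
| 0.3 | 9% | 0.95 | 0.374 | 110 |
| 0.5 | 25% | 0.87 | 0.339 | 133 |
| 0.7 | 49% | 0.71 | 0.280 | 196 |

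**3. Chance imbalance.** The between-arm difference in mean baseline value has standard error sqrt(2/50) = 0.20 SD, a 95% range of about ±0.39 SD. Left out of the model, an imbalance of one standard error moves the estimate by rho × 0.20, which is 0.06, 0.10 or 0.14 SD at rho = 0.3, 0.5 or 0.7. Including the baseline value removes this shift.

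**4. The cessation model behaves differently.** Everyone smokes at entry, so abstinence has no baseline value of its own. Adding a prognostic covariate to a logistic model also does not act as it does in a linear one. Logistic models were simulated with 50 per arm, a true odds ratio of 2 (log 0.693), an assumed control quit rate of 20% and 1,500 runs per setting. They contained treatment alone, or treatment plus one standardised baseline smoking covariate.

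| Prognostic OR per SD (assumed) | Median log OR, without → with | Median SE, without → with | Power, without → with |
|---|---|---|---|
| 1.5 | 0.669 → 0.697 | 0.464 → 0.478 | 0.281 → 0.297 |
| 2.0 | 0.622 → 0.696 | 0.456 → 0.484 | 0.271 → 0.303 |

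The standard error rises slightly, the estimate moves away from the null because the odds ratio is now conditional, and power gains about 1.5 to 3 percentage points. At a 10% control quit rate the pattern is the same and smaller: power goes from 0.165 to 0.169 and from 0.176 to 0.187.

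**The case against.** The best defence has four parts.

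- **Stakes.** The main outcome is the proportion of study completers, which uses no covariates. The effect estimates are declared exploratory and no decision rule hangs on them. This stands and limits the importance. It does not justify a less precise model when the data are to hand, least of all for estimates that will be read for signs of benefit.
- **Deferral.** A full statistical plan is promised, and the article says which covariates the models include without saying that there are no others. That plan could add the baseline values without contradiction. But the article does not leave the covariates open: it publishes a list that reads as applying to every outcome, and that list is what stands until it is corrected.
- **Chance imbalance is not bias.** Correct: randomisation holds and the interval already allows for it. The point is that the interval is wider than it need be.
- **The gain is assumed.** Also correct. Participants who stop smoking fall to zero cigarettes whatever they smoked before, which may weaken the correlation. That is why a range is shown.

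A reader might infer more than the article supports. First, that the quit estimate also loses precision: the simulation shows that the standard error of the log odds ratio rises with adjustment. Second, that the pilot variance will mis-size the main trial: the article nowhere says that it will be used for that. Third, that smoking outcomes are adjusted for mood scores alone: site and PWP are in the models too.

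**Conclusion.** The point holds for CPD and HSI. The stated linear models leave out the outcome's own baseline value although the article says that each measure is summarised at baseline. At assumed partial correlations of 0.3 to 0.7, the intervals are wider than they need be: adjustment would bring them to 0.95 to 0.71 of their width. Typical chance imbalance would move the estimate by 0.06 to 0.14 SD. These figures rest on 50 per arm being followed up, as planned.

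For cessation, the case is only for removing chance imbalance and a small power gain, so adjustment there is optional.

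One uncertainty concerns HSI. Table 3 does not name it, and the nicotine replacement section uses it to grade dependence in the intervention arm only. Its availability at baseline in both arms rests on the general statement that each measure is summarised at baseline. The schedule in Table 1 was not available to check. CPD is named in Table 3.

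The improvement is worth making, but the defect is modest and does not touch the feasibility conclusions.

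**What to change.** Keep site, PWP, GAD-7 and PHQ-9 as stated, and add one sentence to the statistical plan: the CPD model also includes baseline CPD, and the HSI model also includes baseline HSI. PHQ-9 already has its baseline value. Whether PWP should remain in the models is a separate question that this change does not settle.

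For the cessation model, optionally pre-specify one baseline smoking measure: HSI, or CPD if HSI is not recorded at baseline in both arms. State that the resulting odds ratio is conditional on it and that no narrower interval for the log odds ratio is expected.

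The cost is one degree of freedom per model and a stated rule for missing baseline values. If the baseline measures are collected as described, no new data collection is needed.
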